## Abstract

**Introduction:**

Food addiction is characterized by heightened craving and impaired inhibitory control, contributing to compulsive eating and obesity. Existing behavioral and pharmacological interventions often fail to achieve lasting effects. Transcranial alternating current stimulation (tACS), by modulating neural oscillations and connectivity, offers a novel, non-invasive approach for regulating craving-related neural circuits.

**Objectives:**

This study aims to evaluate the effects of fixed-frequency tACS targeting the dorsal lateral prefrontal cortex (DLPFC), anterior cingulate cortex (ACC), and insula on food cravings, inhibitory control, and related neural oscillations. The trial will assess whether tACS can reduce craving intensity and enhance inhibitory performance in individuals with varying degrees of food addiction severity.

**Methods:**

We will conduct a randomized, double-blind, sham-controlled trial involving 175 participants aged 20–55 years, stratified by food addiction status (FA+ vs. FA-) using the Yale Food Addiction Scale (YFAS 2.0). Participants will receive tACS at alpha (10 Hz) or theta (6 Hz) frequency over the DLPFC, ACC, or insula for seven consecutive days. Electroencephalography (EEG) and functional magnetic resonance imaging (fMRI) will be conducted pre- and post-intervention. Primary outcomes include changes in craving intensity and inhibitory control. Secondary outcomes include alterations in neural oscillations and functional connectivity.

**Discussion:**

We hypothesize that theta-tACS over the ACC and insula will enhance inhibitory control and interoceptive awareness, while alpha-tACS over the DLPFC will improve top-down regulatory processes. This protocol aims to clarify the neural mechanisms underlying food cravings and evaluate tACS as a promising intervention for compulsive eating.

## 1 Introduction

Food addiction is characterized by the compulsive overconsumption of highly palatable foods, typically rich in sugar, fat, and salt (Gearhardt et al., 2016). Often overlooked in clinical contexts, FA is increasingly implicated in the global rise of obesity and related metabolic disease, including type 2 diabetes, cardiovascular disorders, and some cancers (Almarshad et al., 2022; Bonaccio et al., 2022; Dinu and Martini, 2023; Soroceanu et al., 2023).

Food addiction shares neurobiological and behavioral features with substance use disorders (SUD), including impaired control, withdrawal, and continued use despite adverse consequences (Gearhardt et al., 2011; Hone-Blanchet and Fecteau, 2014; Gordon et al., 2018; Lampert and Novelle, 2023). Craving intensity in FA is associated with neural mechanisms governing rewards, emotion regulation, and inhibition. Neuroimaging studies have implicated the dorsolateral prefrontal cortex (DLPFC), anterior cingulate cortex (ACC), and insula as core nodes in these craving-related circuits (Parvaz et al., 2011; Koob and Volkow, 2016). Disruption within these networks may contribute to heightened craving and impulsivity (Kim and Lee, 2010; Wiedemann et al., 2021).

Specifically, the desynchronization of theta (4–8 Hz) oscillations in the ACC and insula and alpha (8–12 Hz) oscillations in the DLPFC have been associated with substance craving and addiction behavior (Berke, 2009; Li et al., 2017; Marinkovic and Rosen, 2022; Tian et al., 2024).

Transcranial alternating current stimulation offers a novel, frequency-specific approach to modulate these oscillations. Unlike transcranial direct current stimulation (tDCS) or repetitive transcranial magnetic stimulation (rTMS), tACS can entrain endogenous rhythms and enhance synchronization across distributed neural networks (Herrmann et al., 2013; Vosskuhl et al., 2018). Recent studies suggest that tACS can increase coherence within craving-related networks, particularly in prefrontal regions (Dunlop et al., 2016).

This protocol builds on earlier work showing that neuromodulation can affect craving and self-regulation but overcomes the limitations of static stimulation paradigms by engaging dynamic, frequency-tuned neural circuits (Vosskuhl et al., 2018; Song et al., 2019; Mehta et al., 2023). Through targeting theta and alpha oscillations in functionally distinct regions, we aim to dissect the mechanistic underpinnings of craving modulation and inform the development of targeted neuromodulatory interventions for obesity and compulsive eating behavior.

The primary aim of this study is to evaluate whether tACS targeting the DLPFC, ACC, or insula can modulate craving-related oscillatory activity and enhance inhibitory control in individuals with varying degrees of food addiction. We hypothesize that theta-frequency stimulation of the ACC and insula will strengthen inhibitory control mechanisms and interoceptive awareness, while alpha-frequency stimulation of the DLPFC will enhance top-down cognitive regulation. By investigating these site- and frequency-specific effects, this study seeks to advance our mechanistic understanding of craving-related network dynamics and inform the development of non-invasive neuromodulatory interventions for compulsive eating behavior.

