## 2 Methods

### 2.1 Study design

This randomized, double-blind, sham-controlled, parallel-group trial is designed to investigate the effects of fixed-frequency transcranial alternating current stimulation (tACS) on food cravings, inhibitory control, and associated neural oscillations. The study includes participants with and without food addiction, classified according to the Yale Food Addiction Scale 2.0 (YFAS 2.0).

Participants classified as food-addicted (FA+) will be randomly assigned to one of four intervention arms: (1) active tACS targeting the anterior cingulate cortex (ACC) at a theta frequency of 6 Hz, (2) active tACS targeting the dorsolateral prefrontal cortex (DLPFC) at an alpha frequency of 10 Hz, (3) active tACS targeting the insula at a theta frequency of 6 Hz, or (4) sham tACS serving as a placebo control.

Participants classified as non-addicted (FA-) will be assigned to a separate fifth group. This group will follow a within-subject, counterbalanced crossover design in which each participant receives both active and sham stimulation across two sessions. Sessions will be scheduled on consecutive days, with a 24-h interval, and the stimulation order randomized to mitigate order effects. This approach enables within-subject comparison of stimulation effects in individuals without food addiction and allows for additional between-group analyses contrasting FA+ and FA- responses. Furthermore, the crossover approach in the FA- group is selected to reduce unnecessary stimulation exposure and focus statistical power on the primary FA+ comparisons, while still enabling exploratory within-subject analyses in non-addicted participants.

This design allows for direct comparisons between active and sham conditions and across cortical targets while also enabling exploration of craving-related network dynamics in the presence and absence of FA.

Randomization will be conducted using a computerized block randomization algorithm, stratified by food addiction status (FA+ vs. FA-). To ensure allocation concealment, the randomization sequence will be generated by a researcher not involved in data collection or analysis. All participants, tACS administrators, and outcome assessors will remain blind to group allocation throughout the study.

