### 2.3 Intervention

Participants will receive tACS targeting one of three cortical regions: the ACC, DLPFC, or insula. These targets were selected based on their involvement in the triadic model of craving, representing the impulsive, reflective, and interoceptive systems, respectively (Christie and Bechara, 2020).

Stimulation will be delivered at fixed frequencies supported by the literature on oscillation-specific effects of tACS. The DLPFC will be stimulated at 10 Hz (alpha frequency), while the ACC and insula will receive 6 Hz (theta frequency) stimulation. This frequency choice aligns with prior findings suggesting functional specificity of alpha oscillations in top-down control and theta oscillations in cognitive conflict and interoception (Stecher et al., 2021; Vogeti et al., 2022; Wischnewski et al., 2023).

The stimulation intensity will vary by region, reflecting anatomical depth and field modeling data. For the DLPFC and ACC, the peak-to-peak current will range between 1.5 and 2 mA. However, due to its deeper cortical location, the insula will be stimulated with higher intensities, between 8 and 9 mA peak-to-peak. This is consistent with recent human studies demonstrating the feasibility and tolerability of higher-output tACS for reaching deep brain structures (Shan et al., 2023; Wischnewski et al., 2023). All sessions will last 20 min and occur once daily over seven consecutive days.

Individualized modeling will be conducted using T1-weighted structural MRI scans to generate finite element models (FEMs). Electrode montages will then be optimized using ROAST (Realistic vOlumetric Approach to Simulate Transcranial electric stimulation) (Huang et al., 2019), allowing simulation of electric field distributions within each participant’s head. The modeling will ensure that target field strengths exceed 0.4 mV/mm, a threshold associated with effective neuromodulation (Wischnewski et al., 2023). If predicted intensities fall below this threshold in any region, montage adjustments will be implemented prior to stimulation. HD-Explore, an online visualization tool, will be used to confirm current flow patterns and facilitate replication by other researchers.

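### Frequency is tied to site, and the higher current to the insula, so differences between active arms cannot be attributed to site or stimulation frequency alone

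*Protocol article*

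**What the plan says.** Section 2.1 randomises FA+ participants to sham or to one of three active arms: "active tACS targeting the anterior cingulate cortex (ACC) at a theta frequency of 6 Hz", "active tACS targeting the dorsolateral prefrontal cortex (DLPFC) at an alpha frequency of 10 Hz" and "active tACS targeting the insula at a theta frequency of 6 Hz". Section 2.3 repeats the pairing: "The DLPFC will be stimulated at 10 Hz (alpha frequency), while the ACC and insula will receive 6 Hz (theta frequency) stimulation". It gives the DLPFC and ACC a peak-to-peak current of 1.5 to 2 mA, whereas "the insula will be stimulated with higher intensities, between 8 and 9 mA peak-to-peak". The individual field models must show more than 0.4 mV/mm at the target. No upper limit and no matching across arms is stated. Sham is described with one electrode placement, F3/F4.

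Three places describe what this design is meant to deliver:

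- Introduction, closing the statement of aims: "By investigating these site- and frequency-specific effects, this study seeks to advance our mechanistic understanding of craving-related network dynamics".
- Section 2.1: "This design allows for direct comparisons between active and sham conditions and across cortical targets".
- Section 3 (Discussion) presents the pairing of frequency with region as a way to learn how particular oscillatory regimes act on separate parts of craving regulation.

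The Abstract adds the hypothesis that "theta-tACS over the ACC and insula will enhance inhibitory control and interoceptive awareness", and the Introduction repeats it. In Section 2.5 the primary craving analysis uses a single group factor, whose levels are the stimulation targets and sham, with Bonferroni-corrected post hoc comparisons.

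**The concern.** A claim about frequency needs at least one site stimulated at more than one frequency, or another way to hold site fixed. A claim about site needs two sites that share the other settings. The three active arms offer neither in clean form, and Section 2.5 labels the arms by target alone. If the DLPFC arm did better than the ACC arm, the stated aim would invite reading this as an effect of alpha over theta or of one region over another. If the insula arm did better than the ACC arm, the result could reflect region, the much higher current, or both. The limitations in Section 3 cover duration, individual variability, the trade-offs of EEG and fMRI, correlational connectivity, the missing washout in the FA- group and the restriction to cortical targets. They do not cover this point.

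**Working it through.** The plan gives no figure for this point. The question is what the arms can identify, so sample size, alpha and power do not enter.

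**Inputs** (Sections 2.1 and 2.3)

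| Arm | Site | Frequency | Peak-to-peak current |
|---|---|---|---|
| ACC | ACC | 6 Hz | 1.5–2 mA |
| DLPFC | DLPFC | 10 Hz | 1.5–2 mA |
| Insula | insula | 6 Hz | 8–9 mA |

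**Step 1: pairwise comparison.**

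- ACC vs DLPFC: site and frequency differ.
- ACC vs insula: site and current differ.
- DLPFC vs insula: site, frequency and current all differ.

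With nominal current counted as a factor, 0 of 3 pairs differ in one factor only. If the higher current is instead treated as part of what it takes to reach the insula, ACC vs insula becomes a single-factor site contrast and the count is 1 of 3. The frequency result is the same under both counts.

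**Step 2: size of the current difference.** The smallest ratio is 8/2 = 4.0, the largest is 9/1.5 = 6.0, and at mid-range it is 8.5/1.75 = 4.9. These are ratios of stated current, not of field at target. The field ratio is unknown, because only the 0.4 mV/mm minimum is given.

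**Step 3: what the arm means contain.** Take the simplest additive model, with no interactions: s_D and s_I are the site effects of DLPFC and insula relative to ACC, φ is the effect of 10 Hz relative to 6 Hz, and κ is the effect of the higher current. Then

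- DLPFC − ACC = s_D + φ
- insula − ACC = s_I + κ
- DLPFC − insula = (s_D + φ) − (s_I + κ)

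Only the sums s_D + φ and s_I + κ ever appear.

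**Step 4: rank check.** Columns are intercept (sham), active, DLPFC site, insula site, 10 Hz, higher current.

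| Arm | Int. | Active | DLPFC | Insula | 10 Hz | High current |
|---|---|---|---|---|---|---|
| Sham | 1 | 0 | 0 | 0 | 0 | 0 |
| ACC | 1 | 1 | 0 | 0 | 0 | 0 |
| DLPFC | 1 | 1 | 1 | 0 | 1 | 0 |
| Insula | 1 | 1 | 0 | 1 | 0 | 1 |

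The DLPFC and 10 Hz columns are identical, and so are the insula and high-current columns. The matrix has rank 4 for 6 parameters. Without the current column it still has rank 4, now for 5 parameters, with frequency aliased with the DLPFC.

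**Step 5: other sources of information.** The FA- crossover cannot separate the factors as described, because Section 2.1 does not state the site or frequency of its active session. The modelled field depends largely on arm, montage and current, so adjusting for it cannot separate 10 Hz from the DLPFC.

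**Step 6: multiplicity.** Section 2.5 does not list the post hoc set. If it is all pairs of the four FA+ arms (an assumption), there are 6 tests, each at 0.05/6 = 0.0083, and 3 of them are the bundled active-active contrasts. Three package-versus-sham tests would each be at 0.05/3 = 0.0167.

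**Step 7: interoceptive awareness.** The listed measures are the S-FCQ, T-FCQ, FCI, YFAS 2.0, CESD-R, Go/No-Go task, EEG, and fMRI with craving ratings. None assesses interoceptive awareness. The nearest planned outcome is fMRI connectivity of the insula, which Section 2.4 assigns to the interoceptive system.

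**The case against.** The strongest reply is that the protocol never claims a factorial design. In the Introduction, the phrase about specific effects refers back to the hypotheses just stated, theta at the ACC and insula and alpha at the DLPFC, and Section 3 calls this a pairing of frequency and region. No hypothesis says that alpha beats theta or that one site beats another. A theory-driven pairing is a legitimate choice, and the higher insula current is explained by depth and field modelling.

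Much of this stands, and it rules out several stronger readings that a reader might infer:

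- *That active-active contrasts are invalid and only active versus sham can be interpreted.* FA+ participants are randomised across all four arms, so package-versus-package contrasts are unbiased. Section 2.1's statement about direct comparisons is true of packages.
- *That nothing frequency-specific can be estimated.* Whether theta changes in a theta arm, or alpha in the alpha arm, each against sham, is estimable from the planned EEG. What is not identified is the effect of stimulation frequency with site held fixed.
- *That it is beyond dispute that no pair isolates a factor.* That count depends on treating nominal current as separate from site (Step 1).
- *That active versus sham is itself a perfect contrast.* Sham is described only with F3/F4 placement, so it may differ from the ACC and insula arms in montage as well.
- *That the interoceptive hypothesis has to go.* A planned neural outcome is available to carry it.

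The reply does not rescue attribution. Calling the bundle a pairing describes it without making its parts separable, and a field minimum does not equalise fields. The aim and Section 3 still speak of site- and frequency-specific effects and of oscillatory regimes without stating this limit.

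**Conclusion.** The point holds in a bounded form. The trial can estimate each site-frequency-current package against sham, and one package against another. It cannot assign an active-active difference to stimulation frequency, because 10 Hz is wholly aliased with the DLPFC; this rests only on the arm definitions and holds at any sample size and under any model of the arm means. Nor can it assign such a difference to site alone. For ACC vs insula that part assumes that a 4- to 6-fold difference in nominal current, with only a minimum field ensured, may matter apart from site. How much it matters cannot be judged from the document.

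The randomised comparisons remain valid, and no change of arms or sample size follows. What changes is the mechanistic conclusion the trial may draw, which is reason enough to correct the text.

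**What to change.** 1. In the aim, Section 2.1 and Section 2.5, define the confirmatory contrasts as each site-frequency-intensity package versus sham in the FA+ arms, with Bonferroni over those three.
2. Label active-active contrasts as exploratory package comparisons that support no claim about site or stimulation frequency alone.
3. Keep the term frequency-specific for EEG band outcomes only, and reword the Introduction's aim and the oscillatory-regime sentence in Section 3 to refer to packages.
4. Add to the limitations that site, frequency and current are bundled, and that sham is described with F3/F4 placement only.
5. Present any analysis using the ROAST-predicted field as descriptive within arms, not as removing the confounding.
6. Restate the interoceptive-awareness hypothesis as the planned insula-connectivity outcome.

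This is mostly rewording, plus a fixed list of three confirmatory contrasts. No stimulation setting, arm or sample size changes. The price is more modest mechanistic claims. If the post hoc set would otherwise have been all six pairs, the per-test level for the package-versus-sham contrasts eases from 0.0083 to 0.0167.

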## 2 Methods

### 2.1 Study design

This randomized, double-blind, sham-controlled, parallel-group trial is designed to investigate the effects of fixed-frequency transcranial alternating current stimulation (tACS) on food cravings, inhibitory control, and associated neural oscillations. The study includes participants with and without food addiction, classified according to the Yale Food Addiction Scale 2.0 (YFAS 2.0).

Participants classified as food-addicted (FA+) will be randomly assigned to one of four intervention arms: (1) active tACS targeting the anterior cingulate cortex (ACC) at a theta frequency of 6 Hz, (2) active tACS targeting the dorsolateral prefrontal cortex (DLPFC) at an alpha frequency of 10 Hz, (3) active tACS targeting the insula at a theta frequency of 6 Hz, or (4) sham tACS serving as a placebo control.

Participants classified as non-addicted (FA-) will be assigned to a separate fifth group. This group will follow a within-subject, counterbalanced crossover design in which each participant receives both active and sham stimulation across two sessions. Sessions will be scheduled on consecutive days, with a 24-h interval, and the stimulation order randomized to mitigate order effects. This approach enables within-subject comparison of stimulation effects in individuals without food addiction and allows for additional between-group analyses contrasting FA+ and FA- responses. Furthermore, the crossover approach in the FA- group is selected to reduce unnecessary stimulation exposure and focus statistical power on the primary FA+ comparisons, while still enabling exploratory within-subject analyses in non-addicted participants.

This design allows for direct comparisons between active and sham conditions and across cortical targets while also enabling exploration of craving-related network dynamics in the presence and absence of FA.

Randomization will be conducted using a computerized block randomization algorithm, stratified by food addiction status (FA+ vs. FA-). To ensure allocation concealment, the randomization sequence will be generated by a researcher not involved in data collection or analysis. All participants, tACS administrators, and outcome assessors will remain blind to group allocation throughout the study.

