### 2.4 Outcome measures

The primary outcomes of this study are changes in food craving intensity and inhibitory control following the tACS intervention. Craving will be assessed using the State Food Craving Questionnaire (S-FCQ) and the Food Craving Inventory (FCI), both administered before and immediately after stimulation sessions on Days 1 and 5 (Figure 1). Inhibitory control will be evaluated using a computerized Go/No-Go task at the same time points. These behavioral measures will provide insight into the acute and cumulative effects of tACS on craving regulation and impulse control.

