**FIGURE 1 F1:**
[figure not shown]
Overview of the study timeline, including screening, intervention, and follow-up phases. This schematic illustrates the flow of participant activities and data collection across all phases of the study. Screening and baseline evaluations (Day 0) include eligibility verification, informed consent, structural MRI, and administration of behavioral questionnaires (YFAS 2.0, T-FCQ, CESD-R). The intervention phase (Days 1–7) involves daily tACS, with EEG performed on Days 1, 5, and 7, and behavioral assessments (S-FCQ, FCI, Go/No-Go task) performed on Days 1, 5, and 8. An fMRI will be performed post-tACS on Day 2. Post-intervention imaging (fMRI) and follow-up behavioral measures occur on Day 8. A follow-up assessment on Day 15 evaluates potential sustained effects and adverse events.

Secondary outcomes will focus on neural mechanisms underlying these behavioral changes. EEG will be recorded immediately before and after stimulation on Days 1, 5, and 7 to capture neurophysiological aftereffects (Figure 1). Key EEG parameters include frequency-specific power changes indicative of entrainment, phase-locking value (PLV), and event-related potentials (ERPs). Data will be analyzed at both sensor and source levels using established pipelines.

Functional magnetic resonance imaging will be used to assess changes in functional connectivity within craving-related neural networks. Imaging will be conducted pre- and post-intervention (Day 0 and Day 8) and will include both resting-state scans and a cue-reactivity paradigm (Figure 1). Connectivity will be examined using seed-based correlation and independent component analysis (ICA), targeting the impulsive (ACC), reflective (DLPFC), and interoceptive (insula) systems, which correspond to the stimulation targets.

Craving-related traits will be assessed using the T-FCQ and the YFAS 2.0, administered at baseline (Day 0), and again during follow-up (Day 15) (Figure 1). These measures will provide a broader understanding of individual differences in craving susceptibility and their potential modulation by tACS.

Finally, follow-up assessments on Day 15 will evaluate whether observed behavioral and neural changes persist beyond the immediate intervention phase. This longitudinal component is designed to assess the sustainability of tACS effects and explore delayed neuroplastic adaptations.

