### 2.5 Data collection and analysis

Behavioral data will be collected at multiple time points to evaluate the impact of tACS on food cravings and inhibitory control. The S-FCQ, FCI, and Go/No-Go task will be administered pre- and post-stimulation on Days 1 and 5, and again on Day 8 to assess short-term changes in craving and impulse regulation (Figure 1). Broader trait-level assessments, including the YFAS 2.0 and the T-FCQ, will be administered at baseline (Day 0) and again during the follow-up session on Day 15 to examine long-term or sustained effects (Figure 1).

Electroencephalographic data will be recorded on Days 1, 5, and 7 (Figure 1) using a 64-channel dry electrode cap following the international 10–20 system. Each EEG session will include 5 min of resting-state recording with eyes open, followed by 5 min of viewing food-related and neutral images. Recordings will be conducted both before and after stimulation to detect aftereffects. EEG data will be acquired using the ANT Neuro system at a sampling rate of 1064 Hz. Impedance will be maintained below 10 kΩ. Signal preprocessing and artifact correction will be performed using standard pipelines in EEGLAB and custom MATLAB scripts. Key neural indices will include spectral power, PLV, and ERPs.

Functional MRI data will be acquired using a Siemens 3T Prisma scanner with a 64-channel head coil. Imaging sessions will occur at baseline (Day 0), immediately post-tACS on Day 2, and again post-intervention (Day 8) (Figure 1). Each session will include an 8-min resting-state scan and a cue-reactivity task involving the passive viewing of highly palatable food and neutral images. The cue task will use a block design format with craving intensity ratings collected after each block. BOLD signal changes will be analyzed using Statistical Parametric Mapping 12 (SPM12) and FMRIB Software Library (FSL), with preprocessing steps including realignment, normalization, and spatial smoothing. Functional connectivity will be assessed using seed-based correlation and ICA approaches, focusing on DLPFC, ACC, and insula as predefined regions of interest.

All adverse events or discomforts related to tACS will be monitored daily throughout the intervention phase. Any participant experiencing persistent adverse effects will be withdrawn from the study and referred for appropriate follow-up care.

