By combining high-resolution EEG and fMRI, this study is positioned to provide a multimodal characterization of how tACS influences both oscillatory activity and large-scale network interactions. EEG will allow for the assessment of immediate entrainment and aftereffects, including changes in spectral power, PLV, and ERPs. fMRI, in turn, will assess the spatial and functional reconfiguration of networks via seed-based connectivity and independent component analysis. Particular attention will be paid to connectivity within and between the DLPFC, ACC, insula, amygdala, and striatum. It is expected that alpha-band tACS applied to the DLPFC will enhance top-down control and strengthen connectivity with subcortical structures involved in rewards regulation, while theta-band stimulation of the ACC and insula may normalize aberrant activity in the impulsive and interoceptive systems. This convergence of oscillatory and connectivity-based evidence may validate tACS as a network-level intervention for food craving regulation.

Moreover, the integration of behavioral data, including validated craving questionnaires and Go/No-Go task performance, will allow for a direct correlation between neurophysiological changes and observable cognitive and affective outcomes. The inclusion of both trait- and state-level craving assessments (T-FCQ, S-FCQ, FCI) strengthens the design by capturing both enduring tendencies and momentary fluctuations in craving behavior. When combined with EEG and fMRI findings, these behavioral metrics will provide a comprehensive, multidimensional index of tACS efficacy.

Despite these strengths, several limitations warrant consideration. The relatively brief intervention duration of seven sessions may not fully capture the long-term potential of tACS to modify eating behaviors. Longitudinal studies with extended intervention periods are needed to examine the durability of neural and behavioral changes. Furthermore, individual variability in tACS responsiveness remains a challenge. Factors such as baseline oscillatory state, cortical anatomy, and skull conductivity can influence current distribution and entrainment efficacy (Saturnino et al., 2017). Although individualized modeling using structural MRI and the ROAST pipeline will optimize electrode placement and predict electric field strength, future research should explore real-time, closed-loop tACS protocols tailored to ongoing neural dynamics.

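### The protocol gives FA- participants two sessions in one place and seven daily sessions in others, and after the first session any FA+ versus FA- contrast mixes food-addiction status with active dose

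*Protocol article*

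**What the plan says.** Section 2.1 randomizes FA+ participants to four parallel arms and puts FA- participants in a fifth group, a counterbalanced crossover in which each person has one active and one sham session. On timing it says: "Sessions will be scheduled on consecutive days, with a 24-h interval, and the stimulation order randomized to mitigate order effects". The reasons given are to avoid unneeded stimulation and to concentrate power on the FA+ comparisons. The FA- within-subject analyses are called exploratory, and the section adds that FA+ and FA- responses can be contrasted. The limitations text in Section 3 repeats the 24-hour spacing, concedes that there is no washout, and undertakes to account for residual effects in the analysis.

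Other places give a different number of sessions, with no exception for FA-:

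- Abstract, Methods: "Participants will receive tACS at alpha (10 Hz) or theta (6 Hz) frequency over the DLPFC, ACC, or insula for seven consecutive days".
- Section 2.3: "All sessions will last 20 min and occur once daily over seven consecutive days".
- Figure 1 legend: "The intervention phase (Days 1–7) involves daily tACS".
- Section 3, as a remark on limitations rather than an instruction: "The relatively brief intervention duration of seven sessions may not fully capture the long-term potential of tACS to modify eating behaviors".

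The article prints one assessment calendar. The Figure 1 legend has daily stimulation "with EEG performed on Days 1, 5, and 7, and behavioral assessments (S-FCQ, FCI, Go/No-Go task) performed on Days 1, 5, and 8". Section 2.4 has the craving questionnaires "both administered before and immediately after stimulation sessions on Days 1 and 5", and Section 2.5 says the behavioural measures "will be administered pre- and post-stimulation on Days 1 and 5, and again on Day 8 to assess short-term changes". Section 2.5 and the legend place fMRI on Days 0, 2 and 8.

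**The concern.** Two stated session counts disagree for the same 35 people. Staff who follow Section 2.3 would give FA- participants the week of stimulation that Section 2.1 set out to spare them. Staff who follow Section 2.1 would stop after two sessions.

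On the two-session reading, the FA+ versus FA- contrast raises a second problem. The active FA+ arms go on accumulating stimulation after FA- has stopped. A difference on Day 5 or Day 8 could reflect addiction status, the number of active sessions, or the time since the last one. The data cannot separate these, and a reader could take a dose effect for an effect of food addiction. The no-washout limitation in Section 3 concerns carryover within FA-, not this imbalance between groups.

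**Working it through.** **Group sizes.** The plan reports no calculation for this contrast. Section 2.2.5 gives 140 FA+ participants in four arms, so 140 / 4 = 35 per arm, and 35 FA- participants; 140 + 35 = 175.

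**Session count.** Section 2.1 gives FA- 1 active + 1 sham = 2. The abstract, Section 2.3 and the Figure 1 legend give 7. None of these three distinguishes FA- from FA+, and the abstract sentence directly follows one describing all 175 participants, FA+ and FA-.

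**Cumulative active sessions.** The article does not say on which days FA- sessions fall; Days 1-2 are assumed.

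| Day | Active FA+ arm | FA+ sham | FA- |
|---|---|---|---|
| 1 | 1 | 0 | 1 (active first) or 0 (sham first) |
| 2 | 2 | 0 | 1 |
| 5 | 5 | 0 | 1 |
| 7 and 8 | 7 | 0 | 1 |

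The groups match only at the first session: active-first FA- with an active FA+ arm at the same target, and sham-first FA- with FA+ sham. From Day 2 no FA+ arm has the FA- dose. In stimulation time the final gap is 7 x 20 = 140 min against 1 x 20 = 20 min. Recency differs too. On Day 8, FA+ is 8 - 7 = 1 day past its last active session, while FA- is 8 - 1 = 7 days (active first) or 8 - 2 = 6 days (active second) past its own.

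**Calendar.** Behaviour is on Days {1, 5, 8}, EEG on {1, 5, 7} and fMRI on {0, 2, 8}. Checking each consecutive pair from 0-1 to 7-8, no pair has the same instrument on both days. With sessions on Days 1-2, behaviour and EEG surround the first session, and the second has only a post-stimulation fMRI. This calendar therefore cannot serve a crossover whose sessions are 24 hours apart.

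**What a dose-matched contrast can detect.** With two groups, two-sided alpha 0.05 and 80% power, the detectable d solves P(|T| > t(0.975, n1 + n2 - 2)) = 0.80, where T is noncentral t with noncentrality d / sqrt(1/n1 + 1/n2). The unit is the SD of one session's pre-to-post change, assumed equal in both groups. Half of 35 gives 17 or 18 active-first FA- participants.

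- 35 vs 17: sqrt(1/35 + 1/17) = 0.296, detectable 0.845 SD.
- 35 vs 18: sqrt(1/35 + 1/18) = 0.290, detectable 0.828 SD.
- After 20% dropout, 28 vs 14: detectable 0.940 SD.
- If FA- were spread over three targets, about 6 active-first each, 35 vs 6: detectable 1.269 SD.

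**The case against.** The strongest reply is that Section 2.1 is the specific rule for FA-, comes with a reason, and is echoed in Section 3, so it should override the general seven-day sentences. That is the likely intention. It makes the conflict one of wording, but three places still tell staff something else, and none carries an exception.

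A reader might infer from the calendar that the crossover has no paired outcome and shrinks to 17 against 18 different people, detecting only 0.98 SD. The documents do not support that. Measures before and after stimulation on Days 1, 5 and 7 presuppose a participant who is stimulated on all those days, so the calendar reads as written for the seven-day arms. A separate FA- schedule may exist in the full protocol, and Figure 1 itself is not shown. What stands is narrower: the one printed calendar cannot serve the crossover, and no other is visible.

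It can also be said that the article specifies no Day 5 or Day 8 FA+ versus FA- test. Section 2.1 only says such contrasts are possible, and the primary model in Section 2.5 has stimulation target and sham as its group factor. That is fair and limits the severity. But the design fixes the dose imbalance, and no later choice of model can remove it.

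Period and sequence terms for the crossover belong in an analysis plan, and Section 3 already promises to deal with residual effects. Their absence here is no fault.

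**Conclusion.** The session-count conflict is literal: two against seven, for 35 of 175 participants. The dose confounding follows from the two-session design. After the first session an active FA+ arm has 2, 5 or 7 active sessions and FA+ sham has 0, against 1 in FA-, so a later difference cannot be attributed to food addiction. The day-by-day figures assume FA- sessions on Days 1-2; with other days they shift, but the match is still limited to the first session.

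The calendar point is secondary and holds only if the printed calendar is meant for FA-.

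Two stronger readings should be resisted. The documents do not show that FA- participants will actually receive seven sessions, only that the text is unreconciled. Nor is the main trial compromised: the FA- within-subject analyses are labelled exploratory, and the randomized comparisons among the 140 FA+ participants are unaffected. Severity is minor to moderate.

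**What to change.** 1. State in the abstract, Section 2.3 and the Figure 1 legend that FA- receives two sessions and is exempt from the seven-day schedule. Name the FA- active target, which Section 2.1 does not give and which any like-for-like contrast needs.
2. In FA-, give the S-FCQ, FCI, Go/No-Go task and EEG before and after both sessions, in place of the Day 5, 7 and 8 behavioural and EEG assessments. If a separate FA- schedule already does this, print it. Say separately which FA- fMRI scans are kept.
3. Limit FA+ versus FA- inference to first-session pre-to-post change under the same condition and target. Label later contrasts descriptive.

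The cost is wording plus moved assessments. Against the printed calendar, each FA- participant would have 2 + 2 = 4 behavioural administrations instead of 2 + 2 + 1 = 5, and 2 x 2 = 4 EEG recordings instead of 3 x 2 = 6. The real price lies in item 3: about 17-18 FA- against 35 FA+ participants, so only large differences are detectable, and the contrast should be presented as exploratory. Using a single FA- target avoids thinning it further.
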